## Abstract

**Background:**

Individuals with metabolic syndrome (MetS) are at a greater risk for developing atherosclerotic cardiovascular disease (ASCVD) than those without MetS, due to underlying endothelial dysfunction, dyslipidemia, and insulin resistance. Exercise is an effective primary and secondary prevention strategy for MetS; however, less than 25% of adults meet the minimum stated public recommendations. Barriers often identified are lack of enjoyment and lack of time. High-intensity functional training (HIFT), a time-efficient modality of exercise, has shown some potential to elicit positive affectivity and elicit increased fitness and improved glucose metabolism. However, the effects of HIFT on dyslipidemia and endothelial dysfunction have not been explored nor have the effects been explored in a population with MetS. Additionally, no studies have investigated the minimal dose of HIFT per week to see clinically meaningful changes in cardiometabolic health. The purpose of this study is to (1) determine the dose-response effect of HIFT on blood lipids, insulin resistance, and endothelial function and (2) determine the dose-response effect of HIFT on body composition, fitness, and perceived enjoyment and intention to continue the exercise.

**Methods/design:**

In this randomized, dose-response trial, participants will undergo a 12-week HIFT intervention of either 1 day/week, 2 days/week, or 3 days/week of supervised, progressive exercise. Outcomes assessed at baseline and post-intervention will be multiple cardiometabolic markers, and fitness. Additionally, the participant’s affective response will be measured after the intervention.

**Discussion:**

The findings of this research will provide evidence on the minimal dose of HIFT per week to see clinically meaningful improvements in the risk factors of MetS, as well as whether this modality is likely to mitigate the barriers to exercise. If an effective dose of HIFT per week is determined and if this modality is perceived positively, it may provide exercise specialists and health care providers a tool to prevent and treat MetS.

**Trial registration:**

ClinicalTrials.gov NCT05001126. August 11, 2021.

## Administrative information

Note: The numbers in curly brackets in this protocol refer to SPIRIT checklist item numbers. The order of items has been modified to group similar items (see http://www.equator-network.org/reporting-guidelines/spirit-2013-statement-defining-standard-protocol-items-for-clinical-trials/).

## Introduction

### Background and rationale {6a}

Atherosclerotic cardiovascular disease (ASCVD) is the leading cause of death worldwide [1–3]. Individuals with metabolic syndrome (MetS) have a twofold higher risk for developing ASCVD [4] and type 2 diabetes [5]. MetS is present in approximately 34% of the US population, now affecting over 100 million individuals [6], nearly doubling in cases since 2014 [7]. A plethora of evidence exists demonstrating that physical activity and exercise reduce risk factors related to MetS and ASCVD [5, 8–10]. Specifically, high-density lipoprotein cholesterol (HDL-C) and triglycerides (TG) respond favorably in a dose-response manner to exercise intensity and duration [11–17]. Additionally, elevated low-density lipoprotein cholesterol (LDL-C) and total cholesterol (TC) are reduced when aerobic exercise reaches intensities between 75 and 90% maximal oxygen consumption (VO_2max_) [11, 14, 15]. Studies that investigated resistance exercise alone found an independent association with favorable changes in several blood lipid markers (TC, LDL-C, HDL-C, TG, TC:HDL-C) [13, 15, 18]. In addition to favorable blood lipid effects, regular resistance training has been found to improve body composition [19], blood glucose levels [20], and blood pressure [21]. Due to the remarkable evidence demonstrating exercise as an ASCVD and MetS risk mitigator, general exercise recommendations have been published internationally [8, 22].

The combined risk factors of high TG and low HDL-C regularly accompany a metabolic alteration in the size and content of the LDL particle [23]. This has been found to be exacerbated in populations with MetS [24] and believed to be more atherogenic than non-altered LDL particles [25, 26]. This alteration manifests as a greater amount of smaller, delipidated LDL particles, which often present as normal or low LDL-C in blood tests [27]. Different blood metrics exist that count the number of these particles (LDL-P or ApoB) and have been found to be better predictors of ASCVD in diseased populations [28–35]. Limited research exists investigating the favorable effects of exercise training on LDL-P and ApoB. Aerobic exercise at intensities of 65–85% VO_2max_ seems to be beneficial in a volume dose-response manner [17], LDL particle size was improved at higher intensities [36], and additional improvements were found when resistance training was added [37].

Endothelial dysfunction, an early event in the development of ASCVD [38, 39], accompanies MetS and its individual risk factors including hypercholesterolemia [40], hypertension [41], and obesity [42, 43]. Improvements in endothelial function by 2–2.8% translates to a reduction in ASCVD risk by 26–36% [44]. Exercise training improves endothelial function even when changes in risk factors are inconsistent [45, 46]. Specifically, aerobic exercise showed improvements in endothelial function in a dose-response manner with intensity and duration [47, 48]. Resistance exercise, on the contrary, demonstrated adverse effects on vascular stiffness, an independent marker of coronary artery disease associated with endothelial dysfunction [49]. In type 2 diabetics, all exercise modalities improved endothelial function, with the low-to-moderate intensity aerobic subgroups improving the most [50].

Despite the plethora of evidence on the benefits of exercise, only 1 in 4 adults in the world meet publicly communicated recommendations [22, 51]. “Lack of time” and “lack of enjoyment” were the reasons found for low exercise participation [52–54]. High-intensity functional training (HIFT) is an abbreviated modality of exercise that has been shown to elicit exercise enjoyment and adherence [55, 56]. HIFT is defined as a training style (or program) that incorporates functional, multimodal resistance movements, performed at relatively high aerobic intensities in interval sets for time, reps, or rounds [57]. HIFT combines aerobic and functional resistance exercise in one time-efficient workout. Furthermore, this modality uses minimal equipment and space, reducing the barrier of having to use a fitness facility [57]. In at-risk populations, HIFT has improved oxygen capacity, insulin resistance, and muscular strength [58], as well as the MetS *z*-score [59]. In healthy populations, HIFT has also improved cardiorespiratory fitness [60, 61], muscular strength and power [62], and waist circumference and agility [61]. Willis et al. found that a 40-min session of HIFT expended an average of 485 kcal [63]. If performed several times per week, HIFT has the potential to meet the weekly recommended energy expenditure to improve health outcomes [19]. Little is known about the effects of HIFT on blood lipid markers, endothelial function, and other risk factors associated with MetS.

The minimum, beneficial dose of HIFT per week has not been investigated. However, minimal doses of the HIFT components: high-intensity aerobic and resistance exercise, have been explored. High-intensity interval training (HIIT) describes unimodal aerobic exercise, performed in brief, intermittent vigorous bursts, interspersed with periods of rest [64]. HIIT resembles the aerobic component of HIFT. When HIIT is performed a minimum of two times per week, this exercise demonstrated benefits in VO_2peak_, waist circumference, thigh cross-sectional area, and quality of life [65]. Additional improvements in body composition and blood lipids were seen only after HIIT was performed three times per week, indicating an influence of frequency [65]. Resistance training, the other component of HIFT, demonstrated superior hypertrophic outcomes after two times per week versus volume-matched exercise one time per week, also indicating an influence of frequency [66, 67]. Research on the dose effects of resistance training on blood lipids, insulin resistance, and endothelial function is minimal; however, performing resistance training less than 1 h per week is associated with a 29% lower risk of developing MetS [68]. With HIFT being a combination of HIIT and resistance training, which both possess certain dose-response characteristics, investigations are needed to determine the minimum weekly amount of HIFT needed to see improvements in endothelial health, blood lipids, and insulin resistance.

Knowing that exercise is a robust tool for mitigating and even eliminating MetS [10], including beneficial effects on lipid profile [11–18] and endothelial function [44–50], but participation in the public recommendations is poor, research on well-accepted modalities, and the minimal dose of such, is needed. If a regular habit of HIFT is achievable, enjoyable, and elicits improvements in health, then HIFT could be a realistic and viable lifestyle intervention for the primary prevention of MetS. Thus, the aim of this study is to investigate the dose-response effects to differing weekly frequencies of a HIFT intervention on blood lipids, endothelial function, insulin resistance, and exercise enjoyment, in a population of sedentary individuals with MetS.

### Objectives {7}

#### Research hypotheses

There is a volume dose-response effect of HIFT on blood lipids, glucose metabolism, endothelial function, fitness, and body composition.

There is an inverse dose-response effect of HIFT on the perception of “exercise enjoyment” and “intention to continue.”

#### Primary research aim

The primary research aim is to explore the dose effects of 3 different weekly volumes of HIFT on ApoB, TG, and cholesterol content of LDL, VLDL, and HDL particles; fasting insulin; fasting glucose; glycosylated hemoglobin (HbA1c); and endothelial function after a 12-week training program.

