### Outcomes {12}

#### Primary outcomes

##### Blood analysis

Baseline and post-training blood analysis will be measured via venipuncture of the antecubital vein. Five milliliters of blood will be drawn for the lipoprotein metabolism profile (LMPP), 1 mL will be drawn for insulin, 1 mL will be drawn for glucose, 1 mL will be drawn for HbA1c, and 1 mL will be drawn for hematocrit. The LMPP consists of an ApoB count, Lp[a] count, and cholesterol and triglyceride content of each lipoprotein subclass (VLDL, LDL, HDL). Hematocrit is calculated to adjust for plasma volume changes applied to the cholesterol and triglyceride content measures. Glucose and insulin measures will be used to calculate insulin resistance (IR) using the homeostatic model assessment (HOMA) [83, 84]. For each variable, individual change from baseline will be calculated. Data will be aggregated as mean ± standard deviation (SD) for each dose group as well as for male and female subgroups with each dose groups. The mean change ± SD for each variable will be compared between the 3 dose groups and subgroups.

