##### Endothelial function

Baseline and post-training endothelial-dependent vasodilation of the non-dominant forearm will be measured using venous occlusion strain gauge plethysmography (EC6 Strain Gauge Plethysmography System & Rapid Cuff Inflation System, Hokanson Inc., Bellevue, WA). Basal endothelial function will be measured for 5 min. During 5 min of reactive hyperemia, peak forearm blood flow (FBF) and 30-s area under the curve blood flow will be quantified. For each variable, individual change from baseline will be calculated and aggregated as mean ± SD for each dose group and subgroups. The mean ± SD for each variable will be compared between the dose groups and subgroups.

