#### Sample size {14}

The sample size was projected with a change in ApoB as the main outcome variable between HIFT1 and HIFT3. Power calculations (IBM SPSS v25 Armond, NY) assumed a 1:1 equal allocation between HIFT1 and HIFT3. The baseline mean and standard deviations from a previous study [97] and pilot studies for ApoB were ~ 129 ± 25 mg/dL in sedentary adults with elevated cardiometabolic risk. Collectively, using these data, we consider a 15% reduction in ApoB to be clinically meaningful within the HIFT3 group [98]. Assuming a power of 0.90, *α* = 0.05, and an effect size of *d* = 0.80, a paired samples one-tailed *t*-test sample size calculation revealed a sample size of 60 subjects (20 per group) will establish the superiority of HIFT3 versus HIFT1 for pre- to post-differences in the primary outcome ApoB. With an estimated 5% dropout rate, we will recruit 22 subjects/group to obtain the necessary sample size of 60. Therefore, a total of 60 men and women who meet the previously stated inclusion criteria will be recruited and randomized post-baseline assessments into one of the three intervention groups. Data will be collected in cohorts of 12, randomized into intervention groups. This will continue until 20 participants per intervention group have completed the study. This will accommodate dropout within cohorts.

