##### Endothelial function

Endothelial function will be assessed at baseline and 48–72 h after the last exercise bout of the intervention. Fasted, endothelial-dependent vasodilation of the non-dominant arm will be measured using venous occlusion strain gauge plethysmography (EC6 Strain Gauge Plethysmography System & Rapid Cuff Inflation System, Hokanson Inc., Bellevue, WA). To begin, forearm volume will be measured by the water displacement method. Then, the arm will be elevated to the level of their heart, a pneumatic cuff will be placed around the wrist and upper arm, and a strain gauge will be fixed around their lower arm. Once all measuring devices are attached and ready, the contralateral arm will be used to measure HR and BP until stable resting values are obtained (after 15 min of supine quiet rest). Next, basal blood flow will be measured for 5 min. The wrist cuff will be inflated to 220 mmHg, and the upper arm cuff will cycle between 50 and 0 mmHg every 8 and 7 s for the entire 5 min. Then, the brachial artery will be occluded for 5 min at a pressure of 220 mmHg. At the 4-min mark of the occlusion period, the wrist cuff will be inflated to 220 mmHg again. At the end of the occlusion period, the upper arm cuff will be deflated to assess reactive hyperemia for 5 min. Peak forearm blood flow and 60-s hyperemia blood flow will be quantified.

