## Statistical methods

### Statistical methods for primary and secondary outcomes {20a}

Only data from participants who complete ≥ 80% of total exercise intervention and with no noticeable change in eating (statistically different energy consumption and macronutrient distribution) and physical activity habits will be included [97, 99, 100]. All data will be analyzed using the Statistical Package for the Social Sciences (IBM SPSS v25, Armond, NY). Descriptive data if normal will be presented as mean ± SD, or median and interquartile range if not normal; the significance level of all comparative data will be set as *p* ≤ .05, and normality will be assessed using a Kolmogorov-Smirnov test. If normality exists, parametric tests will be used, if normality does not exist, non-parametric tests will be used. Effect sizes (ES) and confidence intervals (CI) will be calculated on the results of all dependent variables. Paired *t*-tests will be used to evaluate the significant differences between pre- and post-measures of both primary and secondary physiological outcomes within each group. A one-way ANOVA will be used to compare the primary and secondary outcomes pre-post mean change between the three groups. When indicated by a significant *F* value, post hoc analysis will be determined using the Bonferroni adjustment for multiple comparisons. The median, mode, and interquartile ranges of the IFIS and PACES data will be calculated for each of the three groups. Should missing data in outcomes occur, a linear-mixed model will be conducted instead of ANOVA as this test accounts for missing data.

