### Methods in analysis to handle protocol non-adherence and any statistical methods to handle missing data {20c}

Participant adherence will be determined by completion of ≥ 80% of total exercise intervention and no noticeable change in eating and physical activity habits, assessed by the Block questionnaires. Should non-adherence occur, outcome variables will be tested using two analysis sets: the intention-to-treat set, considering all randomized participant data regardless of intervention adherence, and the per-protocol set, considering only data from participants who complete ≥ 80% of the total exercise intervention. Analyses will be performed to examine the effect of the different strategies on the conclusions. If intention-to-treat analyses are determined appropriate, reasons for withdrawal will be reported and compared qualitatively. If missing outcome variables occur, imputation of missing data will be considered. To account for missing data, a linear mixed-model analysis will be used to determine if there are differences in the primary outcome variable of ApoB.

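### The protocol contradicts itself on its primary outcome (ApoB alone, or about 9 to 14 measures) and on the hyperaemia window (30 s or 60 s)

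*Protocol article*

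**What the plan says.** **ApoB as the single primary outcome.** Sample size {14} makes change in ApoB the main outcome variable, powers HIFT3 against HIFT1 on it, and attaches the superiority claim to "pre- to post-differences in the primary outcome ApoB". Section {20c}, on non-adherence and missing data, plans a linear mixed model "to determine if there are differences in the primary outcome variable of ApoB".

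**Many primary outcomes.** The Primary research aim covers "ApoB, TG, and cholesterol content of LDL, VLDL, and HDL particles; fasting insulin; fasting glucose; glycosylated hemoglobin (HbA1c); and endothelial function". Outcomes {12} and Plans for assessment {18a} both place the blood analysis and endothelial function under a primary-outcomes heading. The blood analysis described there also includes Lp(a) and HOMA-IR. Sequence generation {16a} and Concealment mechanism {16b} refer to primary endpoints in the plural, and keep the block size and sequences concealed until those have been analysed.

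**Testing rule.** In Statistical methods {20a}, "the significance level of all comparative data will be set as" p ≤ .05. A one-way ANOVA is run on each primary and secondary outcome. Bonferroni is applied only post hoc, after a significant F, to the comparisons between arms within that outcome.

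**Hyperaemia.** Outcomes {12}: "peak forearm blood flow (FBF) and 30-s area under the curve blood flow will be quantified". Plans for assessment {18a}: "Peak forearm blood flow and 60-s hyperemia blood flow will be quantified".

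**The concern.** A primary outcome is the one result on which the trial's main conclusion rests, so the document has to give a single answer to which it is. Here a reader of the sample size section finds one outcome, and a reader of the aims or outcomes sections finds a dozen or so. A later report could present any of them as primary and cite the protocol for it. The Dissemination plan foresees about four papers, which makes consistent labelling more important.

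The testing rule adds to this. If the longer list is taken at its word, every member is tested at the full 5% level, and the one stated adjustment does not reach across outcomes.

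The hyperaemia discrepancy is a smaller, separate matter. Two sections describing the same procedure give different summaries, and neither lists both. Unless one is fixed beforehand, the choice could be made after the results are known. The plural in {16a} and {16b} also leaves it unclear which analyses must be finished before the allocation sequence is released.

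**Working it through.** The protocol states no error rate across outcomes, so there is no figure of its own to reproduce. The inputs are the list of measures and the 0.05 level.

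**1. Counting the measures labelled primary**

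- Narrow reading of the Primary research aim (TG as one item, endothelial function as one): ApoB 1 + TG 1 + cholesterol in LDL, VLDL and HDL 3 + insulin, glucose, HbA1c 3 + endothelial function 1 = 9.
- TG and cholesterol both per particle class, as the blood analysis describes them, with endothelial function as its two flow measures: 1 + 3 + 3 + 3 + 2 = 12.
- Adding Lp(a) and HOMA-IR from the primary blood analysis: 12 + 2 = 14.

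Haematocrit only adjusts for plasma volume and is not counted.

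**2. Chance of at least one significant ANOVA when no outcome truly differs between arms**

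Under independence this is 1 − (1 − 0.05)^k:

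- k = 9: 1 − 0.95^9 = 0.370
- k = 12: 1 − 0.95^12 = 0.460
- k = 14: 1 − 0.95^14 = 0.512

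Independence cannot hold: HOMA-IR is calculated from glucose and insulin, and the lipid measures come from one panel. Correlation lowers these figures, so they are upper values. The protocol gives no correlations, so a common correlation between all outcomes was assumed and varied. The table comes from simulating three arms of 20 with a one-way ANOVA per outcome (F on 2 and 57 degrees of freedom), 20,000 runs per cell.

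| Assumed correlation | k = 9 | k = 12 | k = 14 |
|---|---|---|---|
| 0 (check) | 0.366 | 0.466 | 0.515 |
| 0.3 | 0.335 | 0.404 | 0.449 |
| 0.5 | 0.271 | 0.325 | 0.353 |
| 0.7 | 0.214 | 0.242 | 0.256 |
| 0.9 | 0.132 | 0.141 | 0.149 |

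The zero-correlation row agrees with the formula to within simulation error. For 12 to 14 measures the range is about 14% to 45%.

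**3. The two ways to make the text consistent**

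- ApoB alone as primary: one primary ANOVA, and the level stays at 0.05.
- All 12 to 14 kept as primary with Bonferroni across outcomes: 0.05/12 = 0.0042 to 0.05/14 = 0.0036 per test. A two-sided independent-groups t-test with d = 0.80 and power 0.90 then needs 56 to 58 per group. The same test at 0.05 needs 34, so the adjustment itself accounts for 56 − 34 = 22 to 58 − 34 = 24 per group. The plan has 20 per group.

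**4. Hyperaemia**

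Both sections describe venous occlusion plethysmography of the non-dominant forearm with 5 minutes of reactive hyperaemia, and both list peak forearm flow. They differ on the second measure: an area under the curve over 30 s, against hyperaemia flow over 60 s with no area under the curve mentioned.

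**The case against.** The strongest reply is that the trial is labelled exploratory and its aim is worded as exploration, so adjustment across outcomes is not automatically required. A multiplicity strategy may also sit in an analysis plan that is not shown. Part of this stands: the absence of such a strategy would not be a finding by itself. But the exploratory label does not turn a single primary outcome into a dozen, and it sits badly beside a superiority claim for ApoB. Nor could an analysis plan make the aims agree with the sample size section, or 30 s agree with 60 s.

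A second reply is that ApoB is plainly the anchor: it alone is powered and given a superiority claim, and the long list is a primary domain around it. This is fair, and it rules out some stronger readings:

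- A reader might infer that the primary outcome is wholly undetermined, or that success may be declared on whichever measure reaches significance. The protocol states no such rule, and the superiority wording concerns ApoB only.
- A reader might take 46% to 51% as the trial's false-positive rate. Those are independence figures for correlated markers, and they apply only if the whole list is treated as primary.
- A reader might add the within-arm paired tests (3 arms × 14 measures = 42 tests, 42 × 0.05 = 2.1 expected false positives). That presumes no change in any arm, although all three arms exercise, and it says nothing about comparisons between arms.
- A reader might call the two hyperaemia descriptions rival definitions. They may be different summaries or an editing slip. What is established is that the sections disagree.

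**Conclusion.** The contradiction is real and lies in the stated text. ApoB is the single primary outcome in {14} and {20c}. About 9 to 14 measures are primary in the aim, {12} and {18a}, with plural primary endpoints in {16a} and {16b}. Section {20a} tests each at p ≤ .05 with no control across outcomes.

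If the full list is treated as primary, the chance of at least one false-positive between-arm result is at most 46% (12 measures) to 51% (14), and about 14% to 45% for assumed common correlations of 0.9 to 0.3. These figures rest on the count chosen, no true difference between arms on any measure, and correlations that the protocol does not supply. If ApoB is the sole primary outcome, this inflation does not arise.

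The 30-s against 60-s mismatch is a separate inconsistency with no error rate attached. Both points should be corrected before data are seen.

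**What to change.** - Name between-group change in ApoB as the sole primary outcome in the Primary research aim, Outcomes {12}, Sequence generation {16a}, Concealment mechanism {16b} and Plans for assessment {18a}, to match Sample size {14} and section {20c}. Changing only the aim and {12} would leave the contradiction standing in the other three sections.
- List the other lipid measures, the glycaemic measures and endothelial function as secondary outcomes, reported with confidence intervals and without confirmatory claims.
- Specify one hyperaemia summary (area under the curve or flow) and one window, in identical words in {12} and {18a}, before any data are seen.

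Cost: the other markers lose the primary label, although all are still measured and reported. Because study objectives change, the protocol's own rule in {25} requires a formal amendment approved by the ethics bodies of both institutions. No extra participants or measurements are needed.
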